## Background

Antimicrobial Stewardship (AMS) describes a diverse set of programmes and projects aimed at reducing inappropriate antimicrobial use [1]. Improving AMS is a global health priority in order to maximise treatment and prevention of infections, minimise the spread of Antimicrobial Resistance (AMR), and minimise adverse drug events [2]. In 2019 it was estimated 4.95 million deaths globally were associated with AMR [3], and this is predicted to rise to 10 million deaths annually with a cumulative $100 trillion loss of economic output by 2050 [4].

The intensive care unit (ICU) is an important in-hospital setting in which to optimise AMS since an estimated 70% of ICU patients receive antimicrobials during the intensive care admission. An estimated 50% of ICU patients have diagnosed bacterial infections (of which many are hospital-acquired infections), many patients are admitted to the ICU having already received often more than one antimicrobial agent, and many others have septic shock where rapid administration of broad-spectrum antibiotics is both indicated and common [1, 5, 6]. As a consequence of the acute illness of ICU patients, concomitant ICU therapies which suppress immunity and the high healthcare-worker to patient ratio risking cross infection, there is a high density of multi-drug-resistant organisms in ICU [7]. These population, treatment process and environmental factors makes delivering appropriate antimicrobial therapy in ICU settings challenging. Approximately 40–50% of ICU antimicrobial prescribing is ‘inappropriate’ [5, 8, 9], and is associated with increased ICU mortality [10]. The most common examples of antimicrobial inappropriateness include: overprescribing (antimicrobials prescribed which are not needed); unnecessary combination therapy; wrong antibiotic choice for documented indication; incorrect route of administration (e.g. parenteral instead of enteral); and duration of therapy longer than necessary [11, 12].

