### Intervention: structured review of antimicrobial prescribing appropriateness

#### Rationale

Structured multidisciplinary antimicrobial prescription reviews have been demonstrated to reduce overall antimicrobial utilisation and prescription redundancy (‘two or more agents intentionally, or unintentionally duplicating treatment’) [33, 34]. Redundancy directly impacts antimicrobial resistance rates and escalates healthcare costs for patients, providers and payers [22, 35]. Structured prescribing reviews promote: focused antimicrobial agent choice in response to microbiological evidence; avoidance and/or de-escalation of antimicrobial prescriptions where patients are found to have non-infectious syndromes or colonisation; utilisation of enteral routes of administration where appropriate, and avoidance of duplication of prescriptions [36]. Such interventions have appeal in the ICU setting where, in addition to patients with confirmed infection, many patients also present with acute inflammatory syndromes following surgery, injury, or in exacerbations of chronic disease, resulting in rapid commencement of antimicrobials. These prescriptions often occur prior to ICU admission, and once started, are difficult to de-escalate [5]. The WHO toolkit for AMS in LMICs prioritises reducing unnecessary and redundant antimicrobial prescribing and consists of four key steps for review: choosing therapies to best suit indications; optimising routes of administration; limiting therapy duration; and documenting a planned stop date [11].

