#### Conduct of review

Participating ICU teams will be required to undertake a structured review of each antimicrobial prescription for all patients receiving antimicrobials. Reviewing prescriptions allows their appropriateness to be reconsidered in the context of emerging clinical and/or microbiological data [37]. The review should be completed within 48 h of a new prescription being commenced, or at ICU admission where pre-ICU antimicrobial prescriptions exist. The review will necessitate documentation of the four key steps as defined by the WHO: indication (in relation to pre-existing local guidelines), route (e.g. parenteral or enteral), expected duration of therapy and intended stop date (including escalation or de-escalation discussions). It will also necessitate documentation of any changes (or lack thereof) made to the prescription, including: the choice of drug, route of administration and duration of treatment. The reviewing ICU team will consider the choice of therapy in relation to the known or assumed indication, the dose in relation to local ICU antimicrobial guidelines, the route of administration, and whether escalation to parenteral, or de-escalation to enteral route (and related dosing and duration adjustments) are warranted. Given the rapidly changing clinical status of critically ill patients, and emerging clinical and/or microbiological data during the ICU stay, it is anticipated that patients may receive more than one review during their ICU encounter. ICUs’ existing antimicrobial guidelines for the management of infections in critically ill patients will be utilised.

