### Implementation

#### Design

A multifaceted approach has been shown to be a critical condition for success of implementation in various settings [39]. Combining implementation strategies has been demonstrated to have a greater success of both implementation and intervention effectiveness when compared to the use of single strategies alone [40]. This project will combine three implementation strategies that have been reported to have been both effective in implementing practice change in critical care in LMICs in a recent systematic review [39], and leverage existing infrastructure already operational in the CQR networks [41, 42]. These strategies are described below and summarised in Table 1.

**Table 1 Tab1:** Implementation strategies

QI strategy	Description
1 Protocolised review	Agreement and documentation of a local protocol for structured antimicrobial review (‘the intervention’) in the ICU
2 CQR enabled audit and feedback	CQR report of audit data on implementation of the prescribing review and on prescribing indicators will be available to each ICU. The A&F implementation strategy will augment the existing audit and feedback mechanism which is part of CQR participation. **The existing monthly CQR report has data on:** Proportion of patients receiving one or more antimicrobials (APR), Duration of therapy (DOT) Case mix, care processes and clinical outcomes (Length of Stay, Mechanical Ventilation, mortality). **Additional data collected for audit throughout the project:** Proportion of prescriptions with a documented indication Antimicrobial Density (AD) Culture rates Antimicrobial resistance rates Antimicrobial redundancy rates (as a proportion of total prescriptions). **Additional data collected for audit and feedback weekly during months 4–6:** Proportion of prescriptions reviewed Proportion of reviews within 48 h of prescription commencement Proportion of prescriptions with a documented indication Antimicrobial Density (AD) Proportion of patients with culturing performed Antimicrobial resistance rates (as a proportion of cultures performed). **Ongoing additions to monthly CQR reports beyond month 6** Proportion of prescriptions reviewed

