#### Secondary outcomes: Intervention effectiveness

Intervention effectiveness, defined as the intervention's effect on the relevant care processes and clinical outcomes, will be assessed by reporting ICU trends in *prescription appropriateness* (Antimicrobial density (AD), treatment duration (DOT) and antimicrobial redundancy rate (ARR, % of total prescriptions)), and *processes of care* (proportion of patients for whom cultures are sent, antimicrobial resistance rate, antimicrobial prescribing rate and compliance of prescriptions with local guidelines). Clinical care processes and outcomes (mortality, Length of Stay and duration of organ support) will be also collected as safety endpoints. Unintended and/or adverse consequences of the intervention will also be explored through field notes and interviews with Champions.

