#### Statistics

For the primary outcome, we will describe the proportion of ICUs that achieved ≥ 80% of all three indicators (fidelity, reach and adoption). We will also report these indicators separately. We will compare the proportion achieved in the post-implementation period, as specified in the Table 2, with the baseline assessment, using a McNemar test (Chi-square for repeated measures).

**Table 2 Tab2:** Outcomes

**Outcome**	**Measure and reporting**
Implementation (Primary Outcome)	**Fidelity: **The proportion of prescriptions reviewed as intended (review at 48hrs with documentation of all 4 review components: indication, route, duration and stop date). Reported as a proportion of the number of possible reviews during months 4-6. Numerator: Number of reviews conducted as intended Denominator: Number of prescriptions of antimicrobials Expressed as a %. Binary outcome: success/fail, 80% is threshold. Proportion of weekly A&F report meetings held from month 4 until the time of adoption (Number of meetings/12, expressed as a %) (not in composite outcome)
	**Reach: **Proportion of eligible patients who received a review during months 4-6 Numerator: Number of patients that received at least 1 prescription review Denominator: Number of eligible patients Expressed as a % Binary outcome: success/fail, 80% is threshold. Proportion of eligible staff that receive education (expressed as a %; eligible staff defined prospectively by Champion) (not in composite outcome)
	**Adoption**: Proportion of prescriptions reviewed as intended during month 7 Numerator: Number of prescriptions of antimicrobials reviewed Denominator: Number of prescriptions of antimicrobials Expressed as a % Binary outcome: success/fail, 80% is threshold.
Intervention effectiveness (secondary outcomes)	**Appropriateness of prescriptions:** Antimicrobial Density (AD) Duration of Therapy (DOT) Antimicrobial Redundancy Rate (ARR)
	**Antimicrobial care processes:** Does the drug Duration exceed the Stop date? Antimicrobial resistance rate (% of patients that have an multidrug resistant pathogen identified) Antimicrobial prescribing rate (% of all patients) Count of cultures taken and reported as a proportion of the population on antimicrobials.

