For the secondary outcomes, we will perform an interrupted times series analysis. We will observe the weekly temporal resolution of each indicator and set the model to account for the natural/secular time trend, implementation of the intervention (level change) and the trend after implementation (slope change). We will account for auto-correlations. The model applied will depend on the data, but we will evaluate ARIMA models, segmented regressions and Holt-Winters additive model to evaluate the best model for the times series. Counts of actions recorded in response to the review will be described. The code lists for the primary and the secondary outcomes, and definitions for indicators of quality will be developed and published in advance of data collection.

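### The resistance rate in Table 2 does not separate multidrug-resistant isolates present at ICU admission from those first found later, so part of the outcome cannot respond to the review

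*Protocol article*

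**What the plan says.** Table 2 (Statistics) places the resistance rate among the intervention effectiveness outcomes, in the group on antimicrobial care processes, and words it as "Antimicrobial resistance rate (% of patients that have an multidrug resistant pathogen identified". The section on secondary outcomes (Intervention effectiveness) also lists it: "antimicrobial resistance rate, antimicrobial prescribing rate and compliance of prescriptions with local guidelines". Neither place limits the specimen date or distinguishes organisms present at admission from organisms first found later. Table 1 (Implementation, Design) uses another denominator for the audit report, "Antimicrobial resistance rates (as a proportion of cultures performed", and also gives no timing rule.

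On analysis, the Statistics section says "For the secondary outcomes, we will perform an interrupted times series analysis". The model is to carry a secular trend, a level change and a slope change, with allowance for autocorrelation. No case-mix term is named, although the Data collection section says that source and reason for admission, severity and microbiology are recorded daily.

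On timing, Conduct of review says "The review should be completed within 48 h of a new prescription being commenced". The same sentence adds that prescriptions started before the ICU are to be reviewed at ICU admission.

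On the population, the Background says "many patients are admitted to the ICU having already received often more than one antimicrobial agent" and, of the ICU environment, "there is a high density of multi-drug-resistant organisms in ICU". The Rationale adds, of antimicrobial prescriptions, "These prescriptions often occur prior to ICU admission, and once started, are difficult to de-escalate".

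**The concern.** The outcome is read as evidence on whether the review works, but its numerator has two parts. One is made up of organisms already there when the patient arrives, which no ICU review can alter. The other is made up of organisms first found later in the stay, which better prescribing might reduce. Only the second can carry an effect.

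Mixing them has two costs. The first is sensitivity: the unresponsive cases raise the baseline rate and its variance without adding signal. The second is interpretation: the level of the series also depends on who is admitted. If the proportion of admissions arriving with resistant organisms moves around the start of the review, the model has no term that tells this apart from an effect of the review. Baseline and implementation last about three months each, so there is little series on either side from which to recognise such a shift.

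**Working it through.** **The plan's own figures.** The Recruitment section gives 40 admissions per ICU per month, 75% of patients on antimicrobials, 6 months and 35 ICUs. 40 × 0.75 × 6 = 180 per ICU, and 180 × 35 = 6300. Both stated figures reproduce. The document states no baseline resistance rate, no split by onset and no target effect for this outcome, so what follows is illustration.

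**Structure.** Let m be the percentage of patients positive at admission and a the percentage first positive later. The written outcome is m + a. Let s = m/(m + a). If the review lowers a by a relative r and m is stable:
- absolute change = r × a, whatever the value of m;
- relative change = r × (1 − s).

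**Illustration 1 (assumptions).** Total 20%; s = 40%, 60% or 80%; r = 25%; 35 × 40 × 3 = 4200 patients per period; design effect 2; two-sided 5%; normal approximation with SE = √[2 × (p₁(1−p₁) + p₂(1−p₂))/4200] and power = Φ(|p₁−p₂|/SE − 1.96).

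| s | As written | Relative fall | Power | Later-onset only | Power |
|---|---|---|---|---|---|
| 40% | 20% → 17% | 15% | 71% | 12% → 9% | 89% |
| 60% | 20% → 18% | 10% | 38% | 8% → 6% | 72% |
| 80% | 20% → 19% | 5% | 13% | 4% → 3% | 42% |

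Within each row the absolute fall is the same under both definitions (3, 2 or 1 points). Only the standard error differs: in the first row it is 1.20 points as written and 0.94 points for later-onset cases.

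Taking only patients on antimicrobials (4200 × 0.75 = 3150 per period), power is 58%, 30% and 11% as written, against 79%, 60% and 33%.

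**Illustration 2 (assumptions).** Fix a = 10% and r = 20%, with 3150 per period and no design effect. With no admission cases the change is 10% → 8% and power is 79%. At s = 25%, 50% and 75%, power is 68%, 53% and 37%. The absolute fall is 2.0 points throughout, and the relative fall is 15%, 10% and 5%.

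**Sensitivity to admissions.** A rise in m of r × a between periods hides the effect completely. As a relative rise this is r(1 − s)/s. Under Illustration 1 it is 0.25 × 0.6/0.4 = 37.5%, 0.25 × 0.4/0.6 = 16.7%, and 0.25 × 0.2/0.8 = 6.3%. For example, m going from 12% to 14% while a falls from 8% to 6% leaves the total at 20%.

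**Restricting to patients still in the ICU.** If 70% remain at 48 h (assumption), the later-onset events are unchanged and the denominator is 0.7 × 4200 = 2940. The first row becomes 17.1% → 12.9%, with power 90%; the other two give 73% and 43%. The restriction does not lose the gain.

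These are pooled before-after calculations, not the planned weekly time series. They show direction and relative size, not the trial's actual power.

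**The case against.** The strongest reply is that this is a condensed article. The Statistics section promises code lists and indicator definitions before data collection, and a specimen-timing rule could sit there. That stands as a reason for a modest tone and for placing part of the fix in the code list. It does not remove the point: Table 2 already gives a worded definition that counts any patient with such a pathogen, and that wording suits its use poorly.

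Three stronger readings are tempting, and the documents do not support them.
- A reader might infer that most of the numerator is fixed before any review. No passage gives a share. The Background and Rationale statements concern earlier antimicrobial exposure, not resistant organisms at admission, and the Background also reports that resistant organisms are dense within ICUs, which points to acquisition there.
- A reader might infer that the estimated effect is biased toward zero. On the outcome's own scale, a percentage of patients, a stable admission part does not change the absolute difference.
- A reader might infer that case mix will cancel the effect. A constant admission part is absorbed by the model's level, and a smooth drift by its trend. Cancellation needs a shift near month 4, and nothing in the document predicts one.

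Two further points stand. For patients who arrive on antimicrobials the review is due at admission, so the delay before review is not the issue; the issue is that the organism is already present. And restricting to patients still in the ICU conditions on length of stay, which the Background says stewardship probably shortens.

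**Conclusion.** The concern holds in a limited form. As worded, the resistance rate merges a part that the review cannot affect, of unknown size, with a part that it might. The absolute effect survives. The relative effect shrinks by the factor 1 − s, power falls (from 89% to 71% at s = 40%, and from 42% to 13% at s = 80%, under the assumptions of Illustration 1), and the series is exposed to a shift in admissions near month 4 that the named model terms would not separate from an effect. All of these sizes rest on assumed rates, an assumed effect, an assumed design effect and a simplified comparison.

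The stakes are small. This is one secondary measure. The success criterion in the Analysis section covers redundancy, density and duration of treatment but not resistance, and the primary outcome is unaffected. It is worth correcting because the correction is cheap and can still be made where the definitions are to be fixed.

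**What to change.** In Table 2 and the promised code list, split the resistance outcome by specimen time.

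- **Effectiveness measure:** patients whose first multidrug-resistant isolate comes from a specimen taken after a prespecified time from ICU admission (for example more than 48 h), among patients still in the ICU at that time and without an earlier such isolate. A rate per patient-day at risk is an alternative.
- **Case-mix series:** report isolates from before the cut-off, and the all-patient rate, as separate weekly series. A step in the early-isolate series near month 4 would then be visible.
- **Consistency:** apply the same cut-off and denominator before and after month 4. State the denominator in Table 2 and say how it relates to the per-culture rate in Table 1.

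The cost is a line in Table 2 and an entry in the code list, using microbiology data that the registry already collects daily in months 1–8. The downsides are fewer events in the analysed measure and a denominator conditional on remaining in the ICU at the cut-off. The patient-day version and the retained all-patient series help a reader judge the second.

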### Implementation procedure

The project timelines are illustrated in Fig. 1. Baseline data collection will occur during months 1–3, during which data pertaining to current antimicrobial utilisation and prescribing appropriateness will be captured daily through the CQR, E-CRF and site survey. During this pre-implementation period, the Champions and RAs will undertake online education and receive training from the project team in review processes and orientation to the data in the A&F reports. In parallel, the Champions will engage the wider ICU team to complete the actions described above. Data on existing prescribing practices, which is already captured as part of the CQR report (see Table 1 below) will remain available to the ICUs.

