**Fig. 1 Fig1:**
[figure not shown]
Project timeline

At month 4, ICU teams will commence the protocolised review in their ICU. The Champion will have access to the online enhanced CQR reports, and the online education material will remain available to all ICU team members. Online support for troubleshooting relating to the implementation strategies will be available to the Champions. In addition, voluntary monthly group sessions will be facilitated by the project team from months 4–6, whereby Champions, RAs and other team members will be welcome to join to reflect on their experience and share learning between sites. Daily data collection (CQR and E-CRF) will continue throughout this period. Champions will be interviewed during months 4–6 to explore barriers and facilitators to implementation, adaptations made to both the intervention and its implementation, along with perceptions regarding likely adoption and maintenance (Supplementary File 3).

At the end of month 6, the implementation strategies of online education, the role of Champions, and the RA collecting daily data on review processes will cease. The daily auditing of whether reviews take place will be transferred to the CQR data collectors and reported monthly as part of the CQR report. A second interview will be conducted with Champions following month 6 to explore barriers and facilitators to adoption, and adaptations to the intervention made post-implementation (Supplementary File 4).

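### The interrupted time-series plan defines its effect as a level and slope change but lets the data choose among three model families, one of which (additive Holt-Winters) has no parameter for either

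*Protocol article*

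**What the plan says.** The Statistics section of the protocol article plans an interrupted time-series analysis for the secondary outcomes. On the time unit it says "We will observe the weekly temporal resolution of each indicator". The analysts will "set the model to account for the natural/secular time trend, implementation of the intervention (level change) and the trend after implementation (slope change"), which defines the effect through two parameters. On dependence between weeks it says only "We will account for auto-correlations".

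The choice of model is then left open: "The model applied will depend on the data", and "we will evaluate ARIMA models, segmented regressions and Holt-Winters additive model to evaluate the best model for the times series". The section gives no criterion for best, no default model and no order of preference. What it promises to publish before data collection is code lists and indicator definitions, not the model.

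The timeline is in Implementation procedure: "Baseline data collection will occur during months 1–3" and "At month 4, ICU teams will commence the protocolised review in their ICU". Data collection has registry data running to month 8, and Limitations says implementation is not followed past month 7.

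**The concern.** The same paragraph fixes what the model must estimate and then admits a candidate that cannot estimate it. If Holt-Winters were judged best for a series, there would be no level change or slope change to report for it. The analysts would have to change model after the fact or report a different quantity.

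These outcomes (antimicrobial density, redundancy rate and duration of therapy, with the care-process indicators) carry the article's second objective, the effect of the review on prescribing. Estimates on different scales could not be set side by side. The rule is also weak in itself. Information criteria as software reports them are not on a common scale across these three families, so best has no clear meaning until a rule is given.

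**Working it through.** **The article's own figure.** Its only sample-size figure, under Recruitment, reproduces: 40 admissions × 0.75 × 6 months = 180 per ICU, and 180 × 35 = 6,300. The present point does not depend on it.

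**Number of weekly points** (52/12 = 4.33 weeks per month).
- Baseline, months 1–3: 3 × 4.33 = 13.
- Months 4–7: 4 × 4.33 ≈ 17.
- Total to month 7: 7 × 4.33 ≈ 30; to month 8: 8 × 4.33 ≈ 35.

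**Which candidates hold the two terms.** With D = 1 from implementation at week T, the described model is

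Y(t) = b0 + b1·t + b2·D + b3·(t − T)·D + error,

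where b2 is the level change and b3 the slope change.
- Segmented regression: has b2 and b3 directly.
- ARIMA: has them if step and ramp regressors are added.
- Additive Holt-Winters: has smoothing constants for level, trend and season, plus starting values. Nothing in it refers to T, and the standard form takes no regressors. It has neither b2 nor b3.

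**Holt-Winters fitted to the whole series.** A non-seasonal additive-trend smoother was run on 30 simulated weeks with a true step of −10 (SD 3, 100 runs). Its mean residual was −7.8 in the first intervention week and +0.5 from the fifth week on. The smoother had absorbed the step.

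**Holt as a pre-period forecast.** The contrast is then observed minus forecast, averaged over the post-period. With 17 post weeks numbered 0 to 16, the mean of (t − T) is 8, so this contrast targets b2 + 8·b3, a mixture of the two defined effects. With a pure step of −10 it averaged −10.0, as did the level-change coefficient from segmented regression and from ARIMA. Its SD was 4.0 against about 2.5 for each of those (4.0/2.5 = 1.6 times as large).

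**Seasonality.** A 52-week additive season needs two full cycles for standard initialisation: 2 × 52 = 104 points, against 30 to 35. The fit on 30 points fails for that reason. The article names no period, however, and a 4-week period does fit, on 30 points and on the 13 baseline points.

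**Error rates.** The article states no significance level, so 5% is assumed. Null weekly AR(1) series were simulated, 3,000 per setting, with 13 weeks before and 13 after (one any-of-three run had 17 after). The test is of the level change. Ranges span repeated runs.

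| Rule | Autocorrelation 0 | 0.2 | 0.4 |
|---|---|---|---|
| Any of three models rejects (most favourable pick) | 12% | 15% to 16% | 19% to 21% |
| Model chosen by AIC | 8% | 10% to 11% | 15% to 16% |
| One AR(1) segmented regression, fixed in advance | 9% to 10% | 12% | 14% to 14.5% |

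The three models were ordinary segmented regression, AR(1) segmented regression and a differenced model with step and ramp. AIC chose among all three in one run and between the first two in the other. BIC among the three gave 7.4%, 10.1% and 16.2%. Choice by fit is thus no worse than the fixed AR(1) model at 0 and 0.2, and about 1 to 2 points higher at 0.4. Ordinary segmented regression alone, with no autocorrelation present, rejected in 4.6%.

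Holt-Winters is not in this table. A smaller simulation (250 runs per setting, autocorrelation 0 to 0.6) that let a Holt forecast contrast be picked as well gave 56% to 70%. That contrast alone gave 54% to 65%, partly because its intervals ignore parameter uncertainty, so I put no weight on those figures.

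**The case against.** The strongest reply is that this is a journal article, and that the choice of model, its criterion and its autocorrelation correction are normal content for an SAP that is not shown. That stands against any complaint that the article is silent on the selection rule. It does not answer the mismatch, because the article affirmatively names a family that lacks the terms it has just required. An SAP could narrow the choice, but the published sentence would still need correcting.

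A second reply is that the three families are only to be evaluated, and that one without level and slope terms would sensibly be discarded. That may be the intention, but the text does not say so.

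A reader might also infer more than the documents support:
- That each indicator gets its own model, chosen once results are visible. The text does not say whether one model serves all indicators, whether selection uses only pre-implementation data, or when it happens.
- That free model choice drives a high false-positive rate. The 12% to 21% figures describe picking the most favourable of three models under assumed autocorrelation. The article speaks of the best model for the series, which is a fit criterion, and choice by fit adds little.
- That Holt-Winters yields no effect estimate, or cannot be fitted. It can yield a forecast contrast, and only an annual period, which the article does not specify, fails.

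**Conclusion.** The point holds as a stated inconsistency. The defined effect is a level change and a slope change; one of the three listed families, in its standard form, has no parameter for either and absorbs the change when fitted to the whole series. This conclusion is structural and needs no simulated figure. It assumes standard additive Holt-Winters, since the article describes no regressor extension and no forecast-counterfactual use.

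The error-rate evidence supports a narrower statement. With about 13 baseline weeks, a plain AR(1) correction rejects in roughly 9% to 14% of null series at autocorrelation 0 to 0.4, so most of the excess over 5% comes from the short series and not from choosing among models. The 5% level and the autocorrelation values are assumptions.

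Only the secondary outcomes are touched; the primary composite and its McNemar test are unaffected. The text should be changed, but the point does not threaten the trial's main conclusion.

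**What to change.** Before outcome data are seen, replace the open choice with a named analysis:

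1. Main model for every indicator: segmented regression with secular trend, level change and slope change, which the article already lists.
2. State the autocorrelation method in advance and choose one suited to about 30 weekly points. A plain AR(1) correction does not restore 5%, so a small-sample correction is preferable, for example restricted maximum likelihood with adjusted degrees of freedom. Its error rate should be checked by simulation with 13 baseline weeks before it is adopted.
3. Remove Holt-Winters as a candidate effect model. If a forecast comparison is wanted for description, define it separately and do not call it a level or slope change.
4. Report ARIMA with the same step and ramp terms as a labelled sensitivity analysis, whatever its fit.

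This takes a sentence or two and no extra data. The costs are the loss of freedom to switch models later and, with a small-sample correction, somewhat wider intervals.
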